# Efficacy of acupuncture for chronic prostatitis/chronic pelvic pain syndromes: study protocol for a randomized, sham acupuncture-controlled trial

**DOI:** 10.1186/s12906-016-1428-y

**Published:** 2016-11-07

**Keywords:** Chronic prostatitis/chronic pelvic pain syndrome, Acupuncture, Efficacy, Randomized controlled trial

## Abstract

**Background:**

Chronic prostatitis/chronic pelvic pain syndrome (CP/CPPS) affects many adult men worldwide. The currently available therapies offer little or no proven benefit for CP/CPPS. We designed this study to assess the efficacy of acupuncture therapy for the treatment of CP/CPPS.

**Methods:**

This study is designed as a randomized, sham acupuncture-controlled trial. We will compare patients with CP/CPPS in an acupuncture group and a sham acupuncture group. Sixty-eight patients will be randomly allocated to receive acupuncture or sham acupuncture. The treatments will consist of 30-min sessions, three times weekly, for 8 weeks. The primary outcome measure is change in the weekly mean National Institutes of Health Chronic Prostatitis Symptom Index (NIH-CPSI) total score from baseline through the 8-week treatment period. Secondary measures include the NIH-CPSI subscale scores, the total International Prostate Symptom Score (IPSS), patients’ response rate, and patient satisfaction after treatment. We will also assess changes in the NIH-CPSI total score from baseline at the 20^th^ and 32^nd^ week of follow-up.

**Discussion:**

This is a randomized, sham-controlled trial of acupuncture treatment for CP/CPPS. The results of this trial will provide more evidence on whether acupuncture is efficacious for treating CP/CPPS.

**Trial registration:**

Clinical Trials.gov NCT02588274

## Background

Chronic prostatitis/chronic pelvic pain syndrome (CP/CPPS) is a common prostatic syndrome with a worldwide prevalence of 2 % to 10 % in adult men [1–3]. Based on a survey in China, the prevalence of CP/CPPS-like symptoms among Chinese men is 4.5 % [4]. CP/CPPS can present with a wide range of clinical manifestations; the main symptoms include urogenital pain, lower urinary tract symptoms, psychological issues and sexual dysfunction [5]. Compared with other urological conditions, the aetiologic factors of CP/CPPS are unclear, and its pathophysiological mechanisms are still poorly understood. It is hypothesized that inflammation or abnormal activity of the pelvic nerve and muscle play important roles in this disease [6]. According to the consensus guidelines, there is still no standard treatment for CP/CPPS; as a result, individualized therapy and symptom-based treatment approaches are recommended [5]. The interventions for CP/CPPS include medication (alpha-adrenergic antagonists, antibiotics, pain pharmacotherapies, 5-alpha-reductase inhibitors, and phytotherapy), physiotherapy (biofeedback, acupuncture) and surgical intervention [7–10]. Drugs such as alpha-adrenergic antagonists and antibiotics have been considered the initial treatment options for CP/CPPS, but in most cases, the administration of a single drug does not relieve multiple symptoms [5]. Hence, other approaches to prevent and ameliorate CP/CPPS symptoms are considered essential. Acupuncture may be a currently underestimated option for CP/CPPS treatment. Based on prior research by Lee et al., acupuncture may relieve the pain-related symptoms of CP/CPPS [11]. Thus far, although several well-designed randomized controlled trials (RCTs) related to acupuncture for the treatment of CP/CPPS have been published [12–15], the recommendations for CP/CPPS in current guidelines remain at level 5 (the lowest level) [5]. Therefore, we designed this trial to further assess the efficacy of acupuncture for treating CP/CPPS.

## Methods/design

### Aim

The aim of this study is to evaluate the efficacy of acupuncture in CP/CPPS patients.

### Design

This study is a multi-centre, sham-controlled, randomized trial of acupuncture for the treatment of CP/CPPS that will be conducted in the Guang’anmen Hospital of China Academy of Chinese Medical Sciences and Yantai Hospital of Traditional Chinese Medicine from November 2015 to May 2017. All of the patients will be asked to sign an informed consent form prior to randomization. Blinded evaluators and statisticians will manage all data. We developed this protocol according to the Standard Protocol Items: Recommendations for Interventional Trials (SPIRIT) checklist [16]. This trial protocol has been approved by the Research Ethical Committee of Guang’anmen Hospital of China Academy of Chinese Medical Sciences and Yantai Hospital of Traditional Chinese Medicine, and it has been registered under the identifier NCT02588274 at ClinicalTrials.gov in the USA. Figure 1 provides a study flow chart.

**Fig. 1 Fig1:**
[figure not shown]
Flow chart

### Participants

Sixty-eight patients will be recruited from the Guang’anmen Hospital of Chinese Academy of Chinese Medical Sciences and Yantai Hospital of Traditional Chinese Medicine.

### Inclusion criteria

Patients must meet the diagnostic criteria from the NIH CP/CPPS consensus [17], including the following:History of pain perceived in the prostate region and absence of other lower urinary tract pathology for a minimum of three of the past 6 months. In addition, any associated lower urinary tract symptoms, sexual function, and psychological factors should be addressed. Physical examinations, urine analyses, and urine cultures will be performed for all subjects.Age 18 to 50 yearsNIH Chronic Prostatitis Symptom Index (NIH-CPSI) total score ≥ 15 (scale 0–43, with 0 meaning no symptoms).

### Exclusion criteria

Other urologic diseases, such as acute prostatitis, bacterial prostatitis, benign prostatic hyperplasia (BPH), prostate cancer, urinary tuberculosis, and urinary tract infection. (The 2-glass test will be performed in patients with urinary tract symptoms using their voided bladder 2 (VB2) and VB3, which can provide fairly accurate results and is easy to perform [18].)Serious or acute diseases involving the heart, liver, kidney or blood.Patients receiving acupuncture or medication (including alpha blockers or pain killers) in the week prior to the baseline assessment.

### Recruitment procedures

We will recruit the participants using advertisements in newspapers, on television, and on the Internet. Prospective participants will obtain a good understanding of the trial by reading the advertisement, which will include a brief introduction of the population needed, the contact information of the researchers, and details of the acupuncture intervention and of the comparison (all participants will be informed that there are two acupuncture groups, i.e., a traditional acupuncture group and a sham acupuncture group, in which blunt needles are used to stimulate the acupoint skin, and that they have a 50 % chance of being allocated into either of the two groups). If the patient is eligible and interested in the trial, they will be invited to consult with the study doctors; after the doctors have provided a diagnosis, the patients will be recruited. All of the participants will be required to sign an informed consent form before the trial that will include an introduction of CP/CPPS, the inclusion and exclusion criteria of the trial, and an introduction to the interventions. In addition, participants have the right to withdraw from the trial at any time.

### Randomization

After the participants have completed a baseline evaluation and met the selection criteria, one research assistant, uninvolved with the treatment and data collection, will be responsible for randomly grouping the participants. The acupuncturists will be blinded to the process of randomized assignment. The random sequence will be generated by the Institute of Clinical Pharmacology affiliated to Guang’anmen Hospital of China Academy of Chinese Medical Sciences. Randomization numbers using a block of four will be sealed in a scheduled computer-generated opaque randomization envelope. To ensure that randomization is successfully implemented, the patient’s sequence number will be written outside of the envelope, and a paper-written group name will be inside the envelope. All envelopes will be numbered sequentially. The envelopes will be delivered according to the patients’ screening sequence numbers. Finally, the acupuncturist will be informed of the random numbers and the group assignment by telephone or e-mail.

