In this trial, we aim to clarify the efficacy and safety of acupuncture for treating CP/CPPS. We will calculate the mean NIH-CPSI scores over 8 weeks, and these scores will indicate the weekly efficacy of acupuncture during the 8 weeks of treatment; additionally, the mean value may provide more sufficient evidence for determining whether acupuncture is efficacious for treating CPPS. Furthermore, we will add an expectations scale to explore whether the patients’ expectations have a potential impact on the outcomes of acupuncture treatment. Nevertheless, this study has several limitations, including the small sample size and the unblinded acupuncturists. Due to the use of a sham acupuncture control, a relatively high rate of dropouts might be observed in the control group. Additionally, there is a risk that the blinding method may be unsuccessful in control participants, as the blunt tip needle will not leave puncture holes. Finally, a few participants might be recruited mistakenly due to the overlapping symptoms of CP/CPPS and BPH [41]. Nonetheless, the outcome assessors and patients will be blinded to decrease the potential for bias [42]. We hope that the results of this trial can provide both an evidence-based treatment option for patients suffering from CP/CPPS and an enhanced level of evidence on which to base guideline recommendations.

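### Envelopes are keyed to screening numbers although allocation follows confirmed eligibility, so either the balance of the blocks is not assured or a fixed block of four stays partly predictable (minor)

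*Protocol article*

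**What the plan says.** All but one of these statements stand in the Randomization section of the protocol article.

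- Timing and person: "After the participants have completed a baseline evaluation and met the selection criteria, one research assistant, uninvolved with the treatment and data collection", carries out the grouping.
- Blocks and concealment: "Randomization numbers using a block of four will be sealed in a scheduled computer-generated opaque randomization envelope".
- Labelling: "the patient’s sequence number will be written outside of the envelope, and a paper-written group name will be inside the envelope". Also: "All envelopes will be numbered sequentially".
- Issue rule: "The envelopes will be delivered according to the patients’ screening sequence numbers".
- After assignment, "the acupuncturist will be informed of the random numbers and the group assignment", by telephone or e-mail. The section also says that the acupuncturists are kept blind to the assignment process itself.

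The Discussion lists among the limitations "the small sample size and the unblinded acupuncturists".

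The article gives neither a screen-failure rate nor a rule for the envelope of a man who fails screening.

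**The concern.** Permuted blocks balance the arms only if every place in a block is filled by a randomised patient. A screening number is given to everyone who is screened, including men who then turn out to be ineligible. Some failures are to be expected here. Recruitment is by public advertisement, and entry depends on an NIH-CPSI total of at least 15, an age limit, urine analysis and culture, and a week free of acupuncture and medication. If the envelope follows the screening number, those men leave holes in the blocks.

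The sentence can also be read to mean that eligible men take the next unused envelope in the order in which they were screened. That keeps the blocks whole, but a single block size of four is then at its most predictable, and the acupuncturists are told each assignment as it is made.

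At stake is either the balance that blocking is meant to give or some of the unpredictability of the sequence, in a trial of 68 men. A rule that can be read both ways may also be applied differently from one envelope to the next.

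**Working it through.** **Inputs from the protocol article.** Block size four (Randomization). Two arms with equal chance of allocation (Recruitment procedures). From the sample size section: 34 per group; sham decrease 6.2 with SD 10.3; a second figure of 13.3 with SD 4.5; two-sided 5% level (the sidedness is given with the analysis methods); 90% power; 20% dropout.

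**Assumptions.** The 13.3 is read as the expected decrease in the acupuncture arm, because that reading reproduces the stated sample size. The screen-failure rate is not given, so 10% to 50% is shown. The balance calculation uses one list, for simplicity.

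**Step 1. The plan's own figure.** Difference = 13.3 − 6.2 = 7.1.

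n per arm = (10.3² + 4.5²) × (1.960 + 1.282)² / 7.1² = 26.3, rounded up to 27.

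With dropout: 27 / 0.80 = 33.75, rounded up to 34. This agrees with the plan. In total 68 = 17 × 4, so a single list used in randomisation order ends exactly at 34/34.

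**Step 2. Balance on the literal reading.** Simulation with 20,000 runs: a list of random AABB blocks; each screened man fails independently at the assumed rate; his envelope is skipped; the run stops at 68 randomised.

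| Assumed screen failure | Mean absolute difference in arm size | Chance of a difference of 8 or more (38/30 or worse) |
|---|---|---|
| 0% | 0 | 0% |
| 10% | 2.1 | 1% |
| 20% | 2.9 | 6% |
| 30% | 3.6 | 12% |
| 40% | 4.1 | 18% |
| 50% | 4.6 | 23% |
| Simple randomisation, for reference | 6.5 | 40% |

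**Step 3. What the imbalance costs in power.** Power = Φ(7.1/SE − 1.96), with SE² = 10.3²/n(sham) + 4.5²/n(acupuncture) and each n multiplied by 0.8 for dropout.

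- 34/34: SE² = 106.09/27.2 + 20.25/27.2 = 4.64, power 0.909.
- 38 sham, 30 acupuncture: SE² = 106.09/30.4 + 20.25/24 = 4.33, power 0.927.
- 30 sham, 38 acupuncture: SE² = 106.09/24 + 20.25/30.4 = 5.09, power 0.883.

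**Step 4. Predictability on the other reading (blocks intact).** This assumes someone who knows every earlier allocation and the block size. By place in the block, over the six orderings of AABB:

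- Place 1: best guess right 1/2.
- Place 2: 2/3.
- Place 3: certain if the first two agree (probability 1/3), otherwise 1/2, so 1/3 × 1 + 2/3 × 1/2 = 2/3.
- Place 4: always certain.

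Best guess right: (1/2 + 2/3 + 2/3 + 1)/4 = 0.708. Certain allocations: (1/3 + 1)/4 = 0.333.

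**Step 5. The two effects do not add.** With skipped envelopes the same observer does worse. At 10% to 50% screen failure the certain share falls from about 27% to 8%, and correct guesses from about 68% to 60%. Gaps harm balance and reduce predictability.

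**The case against.** The strongest reply is that the section should be read as a whole. It opens by placing allocation after eligibility, so the later sentence may mean only that eligible men are served in the order they were screened. Nothing says that a failed candidate's envelope is discarded. This is a fair reading and it makes the balance problem conditional. It does not dispose of the point, because it is the reading under which the fixed block of four is most predictable.

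The concealment described is also sound: a separate institute generates the sequence, the envelopes are sealed, opaque and numbered, and the assistant takes no part in treatment or data collection. This stands, and it makes 33% and 71% upper bounds. They need full knowledge of earlier allocations, and they matter only if the person who has that knowledge can influence who enters and when. The article has study doctors making the diagnosis before recruitment and nowhere says that acupuncturists enrol patients.

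Four stronger inferences are tempting, and the document does not support them:

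- *Allocation before eligibility is settled.* On the literal reading the number fixes the group in advance, but the group stays sealed until the criteria are met. Early disclosure is not shown.
- *Publication of the block size exposed the sequence.* The article is dated 7 November 2016 and the trial is to end in May 2017. If that period includes the week-32 visit, the last man had to be randomised by about 19 October 2016 (31 May 2017 less 224 days), before publication.
- *One list covers both centres.* The article does not say so, and a condensed article may leave this to the full protocol.
- *Imbalance and predictability both apply in full.* Step 5 shows that they work against each other.

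Finally, unequal arms are not in themselves a bias, and a fixed block of four is a common choice. Both are true, and they set the size of the point.

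**Conclusion.** The point holds as a minor one. The issue rule is stated in the article, and it does not fit the statement that allocation follows confirmed eligibility unless nobody fails screening. On the literal reading the planned 34/34 split is not assured. The expected difference is about 2 to 5 patients over an assumed 10% to 50% screen failure. Even 38/30 would move power only between 0.883 and 0.927 from 0.909, depending on which arm is larger. On the alternative reading balance is kept, but up to a third of allocations are certain, and the best guess is right 71% of the time, to someone who knows all earlier ones.

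The required sample size is unaffected. No breach of concealment and no selection bias is shown. The balance and power figures rest on the assumed screen-failure range, a single list, and the reading of 13.3 as the acupuncture-arm decrease.

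**What to change.** Replace the issue rule with one that has a single reading. Number the envelopes by order of randomisation, independently of the screening log, and have the assistant open the next one only after eligibility and baseline are recorded. Draw block sizes at random (for example 2, 4 and 6) and do not disclose them to site staff. If recruitment has ended, report which rule was used and what became of the envelopes of men who failed screening.

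The cost is reprinting the list and envelopes for men still to be randomised, with no extra staff or visits. With varied blocks the last block may be left unfinished. The difference this leaves is at most half the largest block, so no more than 3 per list with blocks of up to 6.

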### Interventions and comparison

#### Treatment group

According to records in the ancient Traditional Chinese Medicine work *Huangdi Neijing*, acupuncture points belonging to bladder meridian (BL) have a noticeable effect on urinary disease. Furthermore, spleen meridian (SP), kidney meridian (KI), and liver meridian (LR) intersect at Sanyinjiao (SP 6), one of the most frequently used acupuncture points for urogenital disease [19, 20]. In addition, the treatment was based on the theory of neuroanatomy [10, 21, 22] and consensus among acupuncture experts in Guang’anmen Hospital. Therefore, we chose the following acupuncture points: Zhongliao (BL 33), Shenshu (BL 23), Huiyang (BL 35), and Sanyinjiao (SP 6) (Table 1). After the patients are relaxed and in a prone position, acupuncturists will use 75 % alcohol pads to sterilize the skin around the acupuncture points and then insert steel needles (Huatuo, Suzhou, China 0.3 mm*40 mm/0.3 mm*75 mm) into the acupuncture points. For bilateral Zhongliao (BL 33), the needle will be inserted approximately 50–60 mm with a 45-degree angle. For Huiyang (BL 35), the needle will be inserted approximately 50–60 mm. For Shenshu (BL 23) and Sanyinjiao (SP 6), the needles will be inserted vertically to a depth of 25–30 mm. Acupuncturists will twirl at BL23, BL35 and SP 6 to achieve and enhance the sensation of aches, heaviness or numbness in the area surrounding the inserted needle (known as de qi), and the manipulations will be performed a total of three times during 1 session (every 10 min). For bilateral BL 33, which are located in the 3^rd^ posterior sacral foramina, needles will be inserted without lifting or rotating based on the characteristics of the points. There are 24 treatment sessions after baseline that occur three times a week, and the participants will receive a 30-min treatment each session.

**Table 1 Tab1:** Measurements at different time points

Measurements	baseline	1 week	2 weeks	3 weeks	4 weeks	5 weeks	6 weeks	7 weeks	8 weeks	20 weeks	32 weeks
NIH-CPSI total score	**×**	**×**	**×**	**×**	**×**	**×**	**×**	**×**	**×**	**×**	**×**
NIH-CPSI subscales score	**×**				**×**				**×**	**×**	**×**
IPSS total score	**×**				**×**				**×**	**×**	**×**
Global response assessment	**×**				**×**				**×**	**×**	**×**
Degree of expectation	**×**										
Satisfation									**×**	**×**	**×**

*NIH-CPSI* The National Institutes of Health Chronic Prostatitis Symptom Index, *IPSS* International Prostate Symptom Score

#### Control group

The control group will receive sham acupuncture at the same acupuncture points as the treatment group. The sham needle with a blunt tip used in the control group is similar to the Streitberger needle (Fig. 2 provides a diagram to illustrate the sham acupuncture applied in this trial) [23]. Acupuncturists will gently lift, thrust, and twist the sham needles to simulate the treatment procedure, thus blinding the patients to the intervention. Each acupuncture point will undergo the same twirling motion as the acupuncture group. The duration and frequency of the sessions will be the same as in the acupuncture group. To ensure blinding, the investigators will make appointments with each participant on alternate days to prevent crosstalk between groups. To test the success of the blinding, the participants will be asked to answer the following question after the 4^th^ week treatment: “Do you think you received traditional acupuncture (A) or sham acupuncture (blunt needles used to stimulate the acupoint skin) (B)?” The participants can answer “A”, “B” or “unclear” (these two interventions will be demonstrated before the treatment, and all participants will have a good understanding of both interventions). Any medication usage should be recorded, including the name of the medicine, the dosage and the session. We will compare the proportion of subjects using medicine and the mean days of medication use between the groups.

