### Data collection and quality control

Because nonstandard input of clinical data can contribute to the bias of results, two investigators (to assess the effect of treatment) will independently collect the data using case report forms and then input the data into a computer; this process will ensure the safety and reliability of the data. To confirm the quality of the trial, all acupuncturists will be required to have an official license and more than two years of clinical experience.

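### The real and sham needling instructions conflict at BL 33 and must be reconciled; demonstrating both techniques, and possibly the alternate-day rule, add smaller blinding risks

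*Protocol article*

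**What the plan says.** **Manipulation.** The Treatment group section names twirling at BL 23, BL 35 and SP 6, done three times per session to obtain de qi. For bilateral BL 33, "needles will be inserted without lifting or rotating based on the characteristics of the points". The Control group section uses the same points and states "Acupuncturists will gently lift, thrust, and twist the sham needles to simulate the treatment procedure, thus blinding the patients to the intervention". It excepts no point. Its next sentence promises that every point gets the twirling given in the acupuncture group.

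**Demonstration.** Beside the blinding question asked after week 4 (answers A, B or unclear), the Control group section adds that "these two interventions will be demonstrated before the treatment, and all participants will have a good understanding of both interventions". Recruitment procedures already has all participants told of "a sham acupuncture group, in which blunt needles are used to stimulate the acupoint skin".

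**Scheduling.** The Control group section says "To ensure blinding, the investigators will make appointments with each participant on alternate days to prevent crosstalk between groups". Under Data collection and quality control, "two investigators (to assess the effect of treatment) will independently collect the data using case report forms". The Discussion states that "the outcome assessors and patients will be blinded to decrease the potential for bias", and lists as limitations the unblinded acupuncturists and the chance that blinding fails in controls because blunt needles leave no puncture holes.

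**The concern.** A sham control isolates the effect of penetration only if everything else done to the patient is the same in both arms. If the sham needles are handled differently from the real ones, or if different acupuncturists resolve the conflicting text in different ways, the contrast mixes penetration with manipulation.

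The primary outcome, the NIH-CPSI total score, is self-reported and the acupuncturists know the allocation. Patient blinding is therefore the main protection against biased reporting, with assessor blinding behind it. Teaching patients what separates the two needles puts some strain on the first. A calendar that encodes the arm, if that is what is meant, would put some strain on the second.

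**Working it through.** No arithmetic decides this point, so the statements are set side by side.

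**1. Manipulation, point by point**

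| Point | Real needle | Sham, general instruction | Sham, parity sentence |
|---|---|---|---|
| BL 23 | twirled | lifted, thrust, twisted | twirled as in real arm |
| BL 35 | twirled | lifted, thrust, twisted | twirled as in real arm |
| SP 6 | twirled | lifted, thrust, twisted | twirled as in real arm |
| BL 33 | not lifted, not rotated | lifted, thrust, twisted | as in real arm, so none |

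- *BL 33.* If the parity sentence means matching the real arm, the sham needle is not twirled there, which contradicts the general instruction to twist. If it means that every point is twirled, it misdescribes the real arm, which is not rotated there. Lifting is also excluded for the real needle and prescribed for the sham. No reading satisfies all three statements.
- *BL 23, BL 35, SP 6.* Twirling and twisting agree. Lifting and thrusting are named for the sham only. They are not excluded for the real needle, so this is an asymmetry on paper and not a strict contradiction.
- *Extent.* There is an explicit contradiction at 1 of 4 named points and an asymmetry at the other 3. With three sessions a week for 8 weeks (3 × 8 = 24), any difference would recur over 24 sessions.

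**2. Demonstration**

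- Recruitment tells patients in words that the sham is a blunt needle on the skin and that the chance of either arm is 50 %. The A/B/unclear question restates that description, so it can be answered without a demonstration.
- A demonstration adds cues about what each technique looks like or involves.
- Table 1 has the NIH-CPSI total score reported weekly from week 1 to week 8, after those cues have been given.
- The Discussion counts on the prone position to keep the procedure out of sight. Showing both procedures beforehand works partly against that.

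**3. Alternate days: two readings**

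- *Days assigned by arm.* This fits the stated purpose of keeping the groups apart. Attendance day then reveals the arm to anyone who sees the schedule and learns one patient's allocation. Booking is given to investigators and data collection to two investigators; the article does not say whether these are the same people.
- *Each patient attends every other day.* This fits the words about each participant and roughly fits three sessions a week. Nothing is revealed, but the groups are not kept apart, so the rule does not achieve its stated purpose.

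Only the first reading threatens blinding, and then only that of assessors who can see the calendar.

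**The case against.** **Manipulation.** The parity sentence shows the intent: the same twirling in both arms. The Discussion also gives a reason for handling blunt needles actively, namely to create a sensation of piercing. Each patient receives only one arm, so a difference in handling need not unblind anyone. This stands as far as it goes. A reader might infer that the sham is in fact manipulated differently. The document does not establish that; it shows instructions that cannot all be followed.

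**Demonstration.** The Discussion cites an earlier crossover study by the same group in which most participants could hardly tell this needle from a real one, and it points to the prone position and the choice of points. Patients already know about the blunt needle, so the extra cue is a matter of degree. These arguments limit the concern. They do not remove it, because the Discussion does not say whether both needles were demonstrated in the earlier study. A reader might also infer that the demonstration serves only the guess question, or that the needles are shown side by side just before the outcome is reported. The text says none of this.

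**Scheduling.** Keeping patients from comparing experiences protects patient blinding, and nothing says that patients are told what a given day means. A reader might infer that assessor blinding is lost and that all 68 allocations can be deduced. That would need fixed days per arm, evaluators who see the calendar, and at least one known allocation at each of the two centres. The document states none of these. With a self-reported primary outcome, the evaluators' influence is limited in any case.

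**Conclusion.** The manipulation conflict holds on the text alone. The instructions for real and sham needling cannot all be followed at BL 33, and lifting and thrusting are named for the sham only. As written, the arms may differ by more than penetration. Which manipulation is right is not judged here.

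The demonstration is a secondary, avoidable weakness. It is explicit in the text and gives cues to patients who report the primary outcome themselves, in a trial that already concedes blinding may fail in controls.

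The scheduling point is conditional. It applies only if days are assigned by arm and evaluators can see the schedule; it then bears on assessor blinding, not patient blinding, and its effect on the primary outcome is limited.

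Neither the size nor the direction of any resulting bias can be derived from the document.

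**What to change.** - **Manipulation.** Reconcile the Treatment group and Control group sections so that the procedure at each of the four points is stated once and matches between arms. Cost: wording and a briefing of the acupuncturists.
- **Demonstration.** Replace it with the verbal description already given at recruitment, and keep the A/B/unclear question. Cost: patients may understand the two options slightly less well.
- **Scheduling.** State what alternate days means. If days are assigned by arm, keep the appointment list from the evaluators, or have patients complete the NIH-CPSI themselves and give the evaluators the completed forms. Cost: a small change in how lists and forms are handled.
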